## Methods

### Experimental Design Overview and Aims

This study was conducted as a cluster-randomized effectiveness study in which primary care teams, within sites, were randomized to one of two conditions: proactive case identification followed by adherence counseling and medication management delivered by a clinical pharmacist trained in behavioral counseling approaches (motivational interviewing) or usual care. This study involves the collection and analysis of both quantitative and qualitative data (the latter primarily at VA sites) during a 14 month intervention period. Qualitative data were also collected at VA sites before the intervention to assess how to make the intervention most effective and after the intervention to evaluate the implementation process, attainment, and sustainability.

Randomization occurred at the team level to evaluate the real-world effectiveness of pharmacist-team interactions rather than just the efficacy of pharmacist interactions with selected patients and to minimize cross-over contamination. At three of the study sites, existing primary care teams were randomly assigned to two intervention teams and two usual care (control) teams. At the fourth study site, the existing primary care teams were randomized to one intervention and one usual care team. At the fifth site, where a true team structure didn't exist, two artificial teams were constructed and randomized to one intervention and one usual care team, for a total of 8 intervention and 8 control teams. Each team consisted of primary care providers, their staff, and patients. All sites were recruited before randomization and then block randomized by site in order to minimize differences in baseline characteristics due to site. Randomization was done by random number generator. Thus allocation concealment was achieved at the cluster level.

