### Intervention

The intervention period was defined as the 14 months in which eligible patients were being identified and offered encounters with the pharmacists. Enrollment of patients occurred during months 1-14. Eligibility for the intervention was determined at the beginning of the 14-month intervention period and again at 3, 6, 9, and 12 months. At the start of each quarter, pharmacists received a list of patients with poor blood pressure control and adherence problems or inadequate medication intensification. The list was randomized within 3 blood pressure strata (> = 160, 150-159, 140-149) to allow outreach to the patients with higher blood pressure levels first. The data were then loaded into the tool used by the pharmacists (MMT) described above. Pharmacists were instructed to contact patients in the order that they appeared on their list. At the end of each quarter, if no attempts had yet been made to contact a patient (i.e., the size of the pharmacist's current patient panel was such that the pharmacist did not have time to contact that individual as well as individuals further down the list), that patient was removed from the pharmacist's list.

Prior to being contacted by the pharmacist, patients at the VA sites were notified via a letter mailed by the study team that a pharmacist would be contacting them to invite them to participate in a new clinical program, a customary VA practice for new projects and programs, and therefore required by the governing IRBs. This letter was not required by the IRB governing the KP sites because patients in KP are accustomed to being contacted by the health plan for clinical outreach.

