### Outcome Measures

#### Primary Outcome

The primary outcome is the relative change in systolic blood pressure measurements over time as recorded at the point of care in VA and KP electronic databases (excluding blood pressures measured by the AIM pharmacists). As this is an effectiveness study, change in each group will be assessed by the comparison of a precision weighted average of the values obtained during routine outpatient clinical practice in 6 month windows preceding and following the intervention period. The 6 month windows placed on either side of the intervention period ensure that a positive finding of the study would suggest a persistent effect on BP and not just a transient effect during the intervention. Secondary outcomes are described in Table 1.

**Table 1 T1:** Secondary Outcomes

*Description*	*Time period*	*Planned analyses*
*A1c *Change in the percentage of eligible patients with an average A1c > 8%	6 months preceding and following intervention period	Hierarchical logistic regression with a dichotomous dependent variable indicating whether each patient on a team is in control or not in each of the baseline and post intervention periods. The cluster identifier is the team, and the analysis will be stratified by site with fixed site effects. Using an analogous model, the primary hypothesis will be tested by examining the interaction between the treatment group variable and the time period variable at the laboratory measurement level.

*LDL *Change in the percentage of eligible patients with an LDL-c >100 mg/dl	6 months preceding and following intervention period	[See A1c]

*Medication Adherence *Change in rates of poor adherence (>20% gap days)	12 months preceding and following intervention period	Regression with a logit link and binomial error term

*Medication Intensification *Count of medication intensification events for BP, lipid, and hypoglycemic therapy [intensification event defined as 1) an increase in the dose of at least one medication or 2) the addition of another medication, or both]	During intervention period	Negative binomial regression

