It was felt to be important to use blood pressures obtained through routine care to assess the impact of the intervention, again to maintain comparability to the control group who would otherwise have to be invited for special visits to measure their baseline and post-intervention blood pressures. As the number of measurements may vary and thus provide more or less precise estimates of the two endpoints, it is not possible to simply construct a difference between the average pre- and post BPs. We will use all data when multiple measurements allow us to estimate a change in BP more precisely as well as those observations in which only 1 measurement occurs in each period with weighting to reflect the varying precision of the estimates.

A three-level multilevel model will allow us to do this with the multiple individual BP measurements (both pre and post intervention) at level 1 nested within patient identifier at level 2 and team at level 3. An indicator variable will represent whether the BP is from the pre or post period coded so that the coefficient estimates the change in mean BP for the control group. The coefficient of an indicator variable representing treatment teams will estimate the mean BP difference between treatment and controls in the baseline period. The primary hypothesis will be tested by an interaction term between the treatment group indicator and the time period indicator variables. The multilevel structure of the model will account for the varying precision with which the BP endpoints are estimated and the clustering of patients within teams. Site will be included as a fixed variable.

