#### Analysis for secondary outcomes

In addition to secondary outcomes mentioned in Table 1, we will conduct a cost-effectiveness analysis to determine differences in costs and utilization between the intervention group and control group patients including total medical care costs, costs and utilization by category (e.g., pharmacy, inpatient, outpatient). To test for differences in costs and resource use by treatment and control group status we will use statistical approaches, as previously described, that account for the non-independence among patients receiving care from the same team and within the same system. In addition, since both counts of resource utilization and costs are usually quite skewed, alternative modeling techniques, such as Poisson regression, negative binomial regression or a generalized gamma regression will be used as appropriate. Given the longer-term expected benefits of the intervention in preventing high cost diabetes-related macro- and microvascular events the primary cost-effectiveness analysis will be conducted using a Markov simulation model. This analysis will be conducted from both a health plan/provider perspective and from a societal perspective as recommended by the Consensus Panel on Cost-Effectiveness Analyses in Health and Medicine.

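### The adherence and intensification rows of Table 1 name no team or site term, and intensification is counted over months before patients become eligible

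*Protocol article*

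**What the plan says.** Teams are the randomized unit. Experimental Design Overview and Aims describes teams allocated within site, "for a total of 8 intervention and 8 control teams". Three parts of the article carry this into the analysis:

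- Primary model (Design Issues for analysis and sample size calculations): a three-level model that accounts for "the clustering of patients within teams. Site will be included as a fixed variable".
- Table 1, A1c row: a hierarchical logistic model, with the statement "The cluster identifier is the team, and the analysis will be stratified by site with fixed site effects". The LDL row refers back to it.
- Analysis for secondary outcomes: costs and resource use are to be compared by approaches "that account for the non-independence among patients receiving care from the same team and within the same system".

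The two Table 1 rows that serve Aim 2 read differently. Poor adherence, compared between the 12 months before and the 12 months after the intervention period, is assigned "Regression with a logit link and binomial error term". For the count of intensification events, the window and model together read "During intervention period Negative binomial regression".

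The Intervention section defines that period as the programme's 14 months. On entry it states: "Eligibility for the intervention was determined at the beginning of the 14-month intervention period and again at 3, 6, 9, and 12 months".

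**The concern.** There are two separate problems.

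**Clustering.** Patients on one team share providers and were allocated together, so a model without team treats correlated patients as independent. Every other analysis described in detail names team; these two rows do not. A binomial error or a negative binomial distribution does not repair this. The negative binomial dispersion parameter absorbs extra variation between patients, not correlation among patients on the same team. Intensification is the more exposed outcome: it is provider behaviour, counted in a single period with no baseline subtracted.

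**Counting window.** A patient first listed at month 9 cannot have had contact with the study pharmacist before then. Intensification in months 0 to 9 is nevertheless counted, in both arms, because the window is the programme's calendar period and the row gives no patient-specific start and no offset. Those months add similar numbers of events to both arms and dilute the contrast.

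Aim 2 rests on these two outcomes. The first problem makes tests too liberal and the second makes the intensification effect look too small. They do not cancel.

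**Working it through.** **The plan's own figure.** No sample size or power is given for adherence or intensification. The Sample Size section gives only the primary figure: 4.4 mmHg at power 0.8, with 275 patients per team and an ICC of 0.02. The SD and alpha are not stated, so it can be neither confirmed nor refuted.

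- Design effect: 1 + (275 − 1) × 0.02 = 6.48.
- Effective number per arm: 8 × 275 / 6.48 = 339.5.
- With an assumed two-sided alpha of 0.05, 4.4 = (1.96 + 0.84) × SD × √(2/339.5), which implies an SD of change of about 20.5 mmHg.

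What carries over to Table 1 is the cluster size and, as an upper reference only, the ICC.

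**Clustering.** Let DE = 1 + 274 × ICC. The standard error is understated by a factor √DE, and the true rejection rate of a nominal 5% test is 2 × [1 − Φ(1.96/√DE)].

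| ICC | DE | √DE | True type I error |
|---|---|---|---|
| 0.001 | 1.27 | 1.13 | 8% |
| 0.005 | 2.37 | 1.54 | 20% |
| 0.01 | 3.74 | 1.93 | 31% |
| 0.02 | 6.48 | 2.55 | 44% |

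Only 0.02 stands in the document, as the most pessimistic value for blood pressure; the other ICCs are assumptions that show the range. The formula takes equal team sizes and one value per patient, so it fits intensification best. Adherence is compared before and after, so stable team differences largely cancel and the relevant ICC is that of change.

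**Counting window.** For first eligibility at month e, the share of the window before eligibility is s = e/14. If the rate ratio is 1 before eligibility and RR after it, and the underlying event rate is constant, the full-window ratio is s + (1 − s) × RR. An RR of 1.5 is assumed for illustration.

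| First eligible (month) | s | Ratio when true RR = 1.5 |
|---|---|---|
| 0 | 0% | 1.50 |
| 3 | 21% | 1.39 |
| 6 | 43% | 1.29 |
| 9 | 64% | 1.18 |
| 12 | 86% | 1.07 |

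The entry distribution is not given. Two assumed patterns:

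- Even entry: mean time before eligibility (0 + 3 + 6 + 9 + 12)/5 = 6 months, s = 6/14 = 0.429, ratio 0.429 + 0.571 × 1.5 = 1.29.
- Half at month 0, the rest even: 0.125 × (3 + 6 + 9 + 12) = 3.75 months, s = 3.75/14 = 0.268, ratio 0.268 + 0.732 × 1.5 = 1.37.

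**The case against.** **Silence is not a decision.** The table is a condensed one, and its cells give a link, an error family or a distribution. A reader might infer that the authors chose to ignore clustering. The document does not say so. The cost paragraph refers to approaches already described that allow for team, and the Sample Size section argues at length why clustering matters. This stands as a limit on the claim. What remains is that the table spells out team and site in one row, cross-refers to it in the next, and then names different models without either term; the cost sentence covers costs and resource use only.

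**The 44% is not an estimate for these outcomes.** It uses a blood-pressure ICC that the authors call pessimistic and expect to be well undercut, more so for change. This stands, hence the range. The argument from change helps adherence but not intensification, which has no baseline.

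**The binomial error is not at fault.** A reader might infer that it ignores the pre/post pairing and so adds false precision. It does not: a hierarchical logistic model has the same error, and ignoring positive pairing tends to make the standard error of a treatment-by-period contrast too large.

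**A programme-period count can be deliberate.** Teams were randomized to study how pharmacists work with teams, and the evaluation takes a health center director's view. Prescribing could change before a patient is listed, so it goes too far to say that no earlier event can be due to the programme. This stands as a qualification. The row states no such aim, and the count remains diluted as a measure of the effect on eligible patients.

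**The dilution figures are illustrative.** The first pull takes the existing pool, so entry may be front-loaded. One eligibility route requires no recent blood-pressure intensification, which lowers the event rate just before listing. Both reduce the dilution.

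**Conclusion.** The point holds in two limited parts.

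First, the adherence and intensification rows name neither team nor site, out of line with the rest of the article. If fitted as written, they would understate standard errors. The true type I error would be about 8% at ICC 0.001 and 44% at ICC 0.02; where these outcomes fall in or beyond that range cannot be known from the document. Intensification is the more exposed of the two.

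Second, on the article's own definitions, 0% to 86% of a patient's intensification window precedes eligibility, depending on the cohort. Unless there is team-level spillover, the rate ratio moves toward 1. The size depends on the entry pattern and the true ratio, neither of which is given. This limb weakens a real effect; it does not create a false one.

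The primary systolic blood pressure model names patient, team and site and is not affected.

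**What to change.** - In both rows, state team as the cluster and site as a fixed effect, in line with the A1c row.
- For adherence, add a patient level and test the treatment-by-period interaction.
- For intensification, count events from first eligibility to the end of the intervention period in both arms, with log person-time as offset. Eligibility is already determined for control patients at the quarterly pulls: the secondary blood-pressure slope analysis in Design Issues relies on it to assign their activation dates.
- If a programme-level effect is wanted, keep the full 14-month count as a sensitivity analysis and label it so.

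The cost is a change of analysis wording and wider intervals for two secondary outcomes. No new data are needed.

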**Methods:**

In this cluster-randomized controlled effectiveness study, primary care teams within sites were randomized to a program led by a clinical pharmacist trained in motivational interviewing-based behavioral counseling approaches and authorized to make BP medication changes or to usual care. This study involved the collection of data during a 14-month intervention period in three Department of Veterans Affairs facilities and two Kaiser Permanente Northern California facilities. The clinical pharmacist was supported by clinical information systems that enabled proactive identification of, and outreach to, eligible patients identified on the basis of poor BP control and either medication refill gaps or lack of recent medication intensification. The primary outcome is the relative change in systolic blood pressure (SBP) measurements over time. Secondary outcomes are changes in Hemoglobin A1c, low-density lipoprotein cholesterol (LDL), medication adherence determined from pharmacy refill data, and medication intensification rates.

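### Table 1 compares medication intensification as a during-period count with no pre-intervention value, although the abstract lists it among changes; this leaves chance team differences in the estimate and may cost precision

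*Protocol article*

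**What the plan says.** The Methods part of the abstract states: "Secondary outcomes are changes in Hemoglobin A1c, low-density lipoprotein cholesterol (LDL), medication adherence determined from pharmacy refill data, and medication intensification rates". On the natural reading, the word for change governs the whole list, including intensification.

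Table 1 (Secondary Outcomes, under Outcome Measures) treats its rows differently:

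- **A1c:** "Change in the percentage of eligible patients with an average A1c > 8" per cent, with 6-month windows before and after the intervention period.
- **LDL:** "Change in the percentage of eligible patients with an LDL-c >100 mg/dl", with the same windows and the same analysis.
- **Adherence:** a change in the rate of poor adherence, with 12-month windows before and after.
- **Intensification:** "Count of medication intensification events for BP, lipid, and hypoglycemic therapy", period "During intervention period", analysis "Negative binomial regression". The row names no earlier window, no period term and no baseline term.

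The prior data exist. The Inclusion criteria use 12 months of earlier refill data and judge recent intensification from automated records. The adherence row also needs a 12-month pre-period.

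The Sample Size section argues, for blood pressure, that analysing change removes systematic differences across teams and reduces clustering. The Experimental Design Overview gives 8 intervention and 8 control teams, randomized within five sites.

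**The concern.** Intensification is a prescribing behaviour, and the Background attributes failures of it to providers. The randomized teams are groups of providers with their staff and patients. Teams may therefore differ in how readily they intensify before the program starts. Blocking by site balances differences between sites, but not differences between teams within a site. With 8 teams per arm, those chance differences go into the estimated rate ratio and its standard error.

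Aim 2 asks about the program's effect on the intensity of regimens, one of the two routes by which it is meant to work. At stake is how precisely that effect is estimated, and whether a reader who starts from the abstract expects a change that Table 1 does not define.

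**Working it through.** **The plan's own figure.** The article gives no power for intensification. Its only power statement concerns systolic pressure: 4.4 mmHg at power 0.8, 275 patients per team, ICC 0.02. The design effect is 1 + 274 × 0.02 = 6.48, so the effective size per arm is 2200/6.48 = 339.5. No SD is stated, so the figure cannot be reproduced; by the normal approximation, with an assumed two-sided 5% level, it corresponds to an SD of about 20.5 mmHg. It does not bear on intensification.

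**Inputs for intensification.** From the article: 16 teams, 5 sites, 275 patients per team. Assumed, because the article gives none of them: 1.5 events per patient, patient-level overdispersion 1, between-team SD of the log rate τ = 0.1, 0.2 or 0.3, and team-level pre/during correlation ρ = 0.3, 0.5 or 0.7. The test is two-sided at 5%. Degrees of freedom are 16 − 5 sites − 1 arm = 10 without the baseline and 9 with it.

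**Step 1, no baseline.** Variance of a team's log rate: v = τ² + (1/1.5 + 1)/275 = τ² + 0.00606. SE of the arm contrast: √(2v/8). For τ = 0.2, v = 0.04606 and SE = 0.107. With no program effect, exp(±1.96 SE) gives a 95% range for the arm rate ratio of 0.88-1.13, 0.81-1.23 or 0.74-1.35 for the three values of τ. This is the ordinary sampling range, which a team-clustered standard error covers.

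**Step 2, effect with 80% power.** Solving the noncentral t with 10 df gives log rate ratios of 0.197, 0.334 and 0.482 (rate ratios 1.22, 1.40 and 1.62).

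**Step 3, add a team-level baseline.** τ² becomes τ²(1 − ρ²), with 9 df. For τ = 0.2 and ρ = 0.5: v = 0.04 × 0.75 + 0.00606 = 0.03606, SE = 0.0949, power 88%.

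**Step 4, charge for chance imbalance in the baseline itself.** With so few teams, adjustment inflates the variance by 1 + χ²₁/χ²₁₀, with mean 1 + 1/(10 − 2) = 1.125. In the same example SE = 0.0949 × √1.125 = 0.1007, and power is 84%.

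Power from a starting point of 80% (step 3, then step 4):

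| τ | ρ = 0.3 | ρ = 0.5 | ρ = 0.7 |
|---|---|---|---|
| 0.1 | 81%, 77% | 85%, 81% | 91%, 88% |
| 0.2 | 82%, 78% | 88%, 84% | 95%, 93% |
| 0.3 | 82%, 78% | 88%, 85% | 96%, 94% |

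The second figure in each cell is the one to use. At ρ = 0 it is 74%. If ρ means the correlation of the true team rates, sampling noise in the observed prior rate lowers the ρ = 0.5 figures further, to 79%, 83% and 84%.

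**Change score instead of covariate.** The variance factor relative to the during-only comparison is 2(1 − ρ): 1.4 at 0.3, 1.0 at 0.5 and 0.6 at 0.7. A plain change score gains only when ρ exceeds 0.5.

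**The case against.** A reader might infer that the during-period result is biased, or that it cannot tell a program effect from teams that already intensified more. The article does not support this. Teams were randomized within site, so the comparison is unbiased, and chance team differences are what a team-clustered standard error allows for.

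The Table 1 cell is also terse: it lists no covariates at all, not even site, and the adherence cell is equally bare. Covariates are commonly left to an analysis plan, which is not shown. The row fixes the outcome window, and a baseline covariate would be compatible with that window. This stands against any claim that the plan excludes a baseline. It does not remove the mismatch between abstract and table, both of which are in the article.

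Prior intensification may also predict later intensification poorly. Patients can qualify through having had no recent intensification, which restricts the prior count and may weaken the correlation. As the working shows, the baseline then gains nothing or costs a little. This stands, and it limits the size of the point.

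Finally, a reader might extend the point to the cost analysis, which sets out to "determine differences in costs and utilization between the intervention group and control group patients" and names no pre-period. That section refers back to the clustered methods already described and makes a Markov model the primary cost-effectiveness analysis. Asking for prior costs as covariates there would be a preference, not a correction.

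**Conclusion.** The point holds in a limited form. Intensification is the only Table 1 outcome with no pre-intervention window, the abstract on its natural reading calls it a change, and the earlier pharmacy data are held. The consequence is exposure to chance team differences and a possible loss of precision; validity is not affected.

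The loss cannot be sized from the article. Under the assumed inputs, the baseline is worth roughly −2 to −3 power points at ρ = 0.3, +1 to +5 at 0.5 and +8 to +14 at 0.7. These figures are for a team-level baseline. A patient-level covariate removes team differences only as far as the patient-level relation carries over to teams, so they are a guide and not a forecast. For a secondary process outcome this is a modest improvement at low cost.

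**What to change.** 1. Reconcile the abstract with Table 1, so that both describe intensification in the same way. A baseline covariate does not by itself turn the outcome into a change. If the count is kept, the abstract's wording should follow it.
2. State in the intensification row that the negative binomial model includes, as a covariate, each patient's intensification count in the 12 months before program start. Allow for unequal observation: log observed follow-up time as offset, and the prior count scaled to observed pre-period time. Counting back from program start, not from eligibility, keeps the program from affecting the covariate.
3. A team-mean term for the prior count is optional. With 16 teams it spends one of about 10 degrees of freedom and carries the inflation in step 4.

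The cost is one derived variable and one edited table row, with no new contact with patients. Pre-period coverage will be incomplete for some later entrants: the KP drug-benefit exclusion looks only at the year before each data pull, so for a patient first eligible at month 12 it guarantees nothing before program start. The gain will be small if prior and later intensification are weakly correlated.
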